#### Aim 2a and 2b analyses

We hypothesize that the OTCH program will be effective and that, over time, user-level psychotic symptoms, functioning, and recovery orientation will improve. Tests for treatment differences between the intervention arms on each outcome (symptoms, functioning, and recovery orientation) will be performed using an HLM including an indicator for intervention status, time (baseline, 12, 24 months), and intervention*time. The magnitude and statistical significance of the beta coefficient for the interaction will provide an assessment of the extent to which the change in psychotic symptoms, functioning, and recovery orientation since baseline over time differs by intervention arm.

Based on prior research [43–45], we have hypothesized that service and implementation outcomes at 12 months will mediate the impact of OTCH on clinical outcomes at 24 months. To establish service and implementation outcomes at participant- and provider-level at 12 months as mediators of the OCTH effect on user-level clinical symptoms, functioning, and recovery orientation at 24 months, in addition to finding intervention effects (OCTH vs FEP usual care) as in Aim 1a and Aim 2a, we must also establish that service and implementation outcomes at 12 months are associated with better participant symptoms, functioning, and recovery orientation at 24 months. The mediation effect [46] is estimated by taking the expected value of the total effect of OTCH vs FEP Usual Care on symptoms, functioning, and recovery, and subtracting the direct effect when service and implementation outcomes are considered. This indirect (or mediation) effect of the implementation factors will be estimated and tested by fitting a Structural Equation Model using MPlus version 7.4 which our lead statistician has extensive expertise. We will estimate mediation models that consider one implementation or service mediator at a time, as well as including all indicators of implementation or service simultaneously to identify independent effects. The bootstrapping method (available in Mplus) will be used to obtain standard errors, confidence intervals, and the test for statistical significance [47]. Even in an RCT, the association between the mediator and the outcome can be confounded by other time-varying confounders and recent developments in mediation analysis suggest the need for sensitivity analyses to explore the potential impact of unmeasured confounders. We will perform these sensitivity analyses which provide a range of plausible results that may have been obtained under different assumptions about unmeasured confounders [48].

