For the cluster trial, power was calculated conservatively based on the participation of 270 participants (rather than the full 300 to be enrolled), anticipating a possible participant drop-out of ~10%. We estimated that, with at least 10 clinics in each condition, we will have 80% power to detect a difference in mean outcomes between study conditions with a moderate effect size of Cohen’s *d* = 0.35 following the standard detectible effect size formula for clustered randomized trials [15, 16]. This power calculation was derived assuming an intra-class correlation of 0.05 for outcomes by clinic (15 participants nested within 21 clinics). We also assume an alpha of 0.05 and that all tests are 2-tailed. Previous research has shown interventions like OTCH to have moderate to large effects on implementation and service outcomes, such as medication adherence, service utilization, and engagement in treatment [5, 17]. We have also shown that FEP providers in Chile rely primarily upon medication and are usually not trained to promote shared decision-making, recovery orientation, or person-centered care [9]. Then it is reasonable to anticipate at least moderate (and probably large) effects of OTCH on these indicators of implementation. Finally, evidence for the expected effect on participant-level symptoms and functioning comes from the RAISE Connection Program study, which indicated improvement over 24 months for participants enrolled (e.g., PANSS improvement effect size 0.91, occupational functioning 1.2, and social functioning 0.72) [17]. Power to detect mediation effects (Aim 2b) depends on the size of the effect of intervention on implementation and service outcomes (path a), and the correlation between implementation and services outcomes and participant level symptoms, functioning, and recovery (path b). Based on tabulated recommendations for sample sizes needed to test mediation effects with a sample of size *N*=270 with follow-up data, we have over 80% power to detect a significant mediation effect with path a=.26 and b=.26. Path a is expected to be >0.35 (argued for Aim 1 above), and we expect based on our previous work that there will be at least moderate associations between implementation and clinical outcomes (*r*>0.40), assuming no confounding of mediator-outcome relationship.

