### Data collection

#### For the trial

Table 4 provides a description of all the measures that will be used in the trial. All instruments will be administered at baseline 12 and 24 months. Selection of measures was guided by the PhenX toolkit for clinical measures in early psychosis and key moderators that are known to influence the implementation of evidence-based practices [19]. All measures will be translated into Spanish if a Spanish language version is not available using the WHO guidelines for translating and adapting measures.

**Table 4 Tab4:** Study assessments

	Construct	Group	Measure description	When	Time
Implementation outcomes	Fidelity	Providers, families, and participants	Adapted version of the OTNY fidelity scale. The scale assesses the degree to which FEP services deliver evidence-based practices. Fidelity assessment will be based on providers’ feedback, supervision calls, and site visits. Site visits have been established as a best practice for fidelity assessment [20].	6, 12, 24 months	NA
	Acceptability	Providers	Providers’ attitudes to evidence-based practices will be measured by the *Evidence-Based Practice Attitude Scale* (EBPAS) [21]. The EBPAS consists of 15 items rated on a five-point scale from 0 (“Not at all”) to 4 (“Very great extent”). Range: 0–60 points.	Baseline, 12, 24 months	15 min
	Uptake	Participants	The *CollaboRATE* [22] is a 3-item scale that measures Shared-Decision Making from users’ perspective. Each of the three items is rated on a scale of 0 (“no effort was made”) to 9 (“every effort was made”). Range: 0–27 points.	Baseline, 12, 24 months	5 min
		Providers	The *Shared Decision Making Questionnaire – Physician Version (SDM-Q-Doc)* [23] will be employed to measure SDM at the provider level. This asks the clinician first to enter the health problem the consultation was about and which decision was made. The questionnaire continues with nine items about the steps in the SDM process, scoring at a six point scale that ranges from 0 (completely disagree) to 5 (completely agree). A total score can be calculated by summing the scores of all items. A high score indicates more SDM.	Baseline, 12, 24 months	10 min

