#### Aim 1a and Aim 1b analyses

We have selected 3 measures of implementation (fidelity, acceptability, and uptake) and 3 measures of service outcomes (patient-centeredness, adherence, and retention) that represent the active ingredients of CSC for people with FEP. These six measures reflect care processes that will be fundamental to the implementation of the OTCH program [13]. Tests for treatment differences between the intervention arms on each of the six outcomes will be performed using a hierarchical linear model (HLM) for each outcome including clinic-level random effects to account for clustering of participants within clinics and participant-level random effects to account for repeated measures on the same user over time. The primary fixed effects will be an indicator for intervention status (OTCH, FEP Usual Care), time (12 or 24 months), and intervention*time. The magnitude and statistical significance of the beta coefficients from the HLMs will be used to test whether implementation and service outcomes differ between intervention arms at 12 and 24 months. If descriptive analyses identify any baseline differences between randomized groups of participants at baseline, we will consider adding the respective covariate to the model to adjust for this.

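### Aim 2a tests the arm difference in change from a freely estimated baseline, which is valid but less precise than adjusting for the baseline score already collected

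*Protocol article*

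**What the plan says.** In the protocol article, under Aim 2a and 2b analyses, the tests for the three clinical outcomes are to be "performed using an HLM including an indicator for intervention status, time (baseline, 12, 24 months", together with the interaction of intervention and time. The interaction coefficient is the test, read as the extent to which "the change in psychotic symptoms, functioning, and recovery orientation since baseline over time differs by intervention arm".

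The Aim 1 model is built differently. Its time factor is "time (12 or 24 months), and intervention*time", so baseline is not an outcome level there. The only wording on covariate adjustment also sits in the Aim 1 paragraph. It applies if descriptive analyses show a baseline difference, and then promises only that "we will consider adding the respective covariate to the model to adjust for this". Nothing under Aim 2a commits to a baseline-score covariate.

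The scores exist. The data collection section says "All instruments will be administered at baseline 12 and 24 months", and Table 4 lists PANSS, SRFP and QPR at all three visits.

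**The concern.** An arm main effect with baseline as a level of time gives each arm a free baseline mean, so the interaction is follow-up minus baseline, compared between arms. Treating time as linear does not alter this for complete data: with three equally spaced visits the slope is half the 24-month-minus-baseline difference.

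A change contrast fixes the weight on baseline at 1. When baseline and follow-up are only moderately correlated, that weight is too large and adds noise. A covariate model estimates the weight.

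At stake is the width of the intervals for the three outcomes that carry Aim 2. The mediation analysis of Aim 2b also relies on the Aim 2a effects. With 21 clinics there is little precision to spare, and the gain needs no new data.

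**Working it through.** **Inputs from the sample size section:** 270 participants analysed, 21 clinics, ICC 0.05, d = 0.35, two-sided alpha 0.05. Participants per clinic: m = 270/21 = 12.86.

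**The plan's own power figure, for context.** Design effect = 1 + (12.86 - 1) x 0.05 = 1.593. Power at d = 0.35 for a plain follow-up comparison is about 62%, and the effect detectable with 80% power is (1.96 + 0.84) x sqrt(4 x 1.593/270) = 0.43. The stated 80% at 0.35 is not reproduced. That is a separate matter, and the present point does not depend on it.

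**Assumptions not in the documents:** r, the within-clinic participant correlation between baseline and 24 months, 0.3 to 0.7; c, the correlation of clinic effects over the same period, 0.5 to 1.0 (1.0 is a clinic random intercept only). Outcome variance is 1 at each visit, with complete data.

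**Formulas, per clinic mean:**
- variance: v = 0.05 + 0.95/12.86 = 0.1239
- covariance of baseline and follow-up: k = 0.05c + 0.95r/12.86
- change contrast: 2(v - k)
- adjusted, clinic-level slope treated as known: v - k²/v
- adjusted, individual score only (slope close to r): v - 2rk + r²v
- adjusted, with the clinic mean and its slope estimated: (v - k²/v) x (1 + 1/(21 - 4)), that is x 1.059

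**Worked case, r = 0.5, c = 0.8:** k = 0.0400 + 0.0369 = 0.0769. Change: 2 x (0.1239 - 0.0769) = 0.0939 before rounding. Slope known: 0.1239 - 0.0769²/0.1239 = 0.0761. Individual score: 0.1239 - 0.0769 + 0.25 x 0.1239 = 0.0779. With clinic mean: 0.0761 x 1.059 = 0.0806.

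| r | c | change | slope known (saving) | individual score (saving) | score + clinic mean (saving) |
|---|---|---|---|---|---|
| 0.3 | 0.5 | 0.1534 | 0.1059 (31%) | 0.1067 (30%) | 0.1122 (27%) |
| 0.5 | 0.5 | 0.1239 | 0.0929 (25%) | 0.0929 (25%) | 0.0984 (21%) |
| 0.5 | 0.8 | 0.0939 | 0.0761 (19%) | 0.0779 (17%) | 0.0806 (14%) |
| 0.7 | 0.9 | 0.0543 | 0.0484 (11%) | 0.0492 (9%) | 0.0512 (6%) |
| 0.3 | 1.0 | 0.1034 | 0.0819 (21%) | 0.0917 (11%) | 0.0867 (16%) |
| 0.7 | 1.0 | 0.0443 | 0.0404 (9%) | 0.0422 (5%) | 0.0427 (4%) |

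A simulation of clinic means (40,000 replicates) agrees with the last column to within about one percentage point.

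**Reading the table.** The saving is positive in every row. Across the two models that could be fitted, the standard error of the change contrast is larger by between sqrt(0.0443/0.0427) - 1 = 2% and sqrt(0.1534/0.1067) - 1 = 20%. The clinic mean repays its cost only where clinic effects are much more stable than participant scores (r = 0.3, c = 1.0).

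**Power at d = 0.35** (normal approximation, contrast variance 4/21 times the table entry), change against individual-score adjustment: 54% against 69% at r = 0.3, c = 0.5; 74% against 82% at 0.5, 0.8; 93% against 95% at 0.7, 0.9. In the first case the change analysis does worse than ignoring baseline (62%).

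**The case against.** The strongest counter-argument concerns recruitment. Under Randomization, clinics are allocated and directors told at the start of the project. Under Recruitment, a clinic provider approaches participants later, the consent forms differ by arm, and baseline is measured after consent. Baseline means may therefore differ systematically between arms. Free baseline means allow for that. This stands. A reader might infer that the stated model costs precision and gives nothing back, or that forcing a common baseline mean is an equally good remedy. The documents support neither.

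Second, the stated contrast is a standard analysis, unbiased under randomisation, and it matches the hypothesis about change. This also stands. A reader might infer an error of validity, but there is none.

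Third, the article is condensed and the analysis plan is not shown, so covariates may be settled there. This stands only in part. The article names the tested coefficient, and that coefficient is a difference in change. Adding a time-constant covariate while baseline remains an outcome level shifts all visits of a participant equally and, with complete data, leaves the change contrast as it was. The conditional adjustment wording under Aim 1 would not recover the precision.

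Fourth, the outcomes are secondary, and at high correlations the gain is small. That limits the weight of the point.

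**Conclusion.** The point holds as one of efficiency. The stated Aim 2a analysis gives up roughly 4-30% of variance compared with baseline adjustment (about 5-30% with the individual score alone, 4-27% with the clinic mean added). This is for ICC 0.05, 270 participants in 21 clinics, participant correlation 0.3-0.7 and clinic correlation 0.5-1.0. The direction was the same in every case examined, but the size rests on correlations that the documents do not supply.

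A reader might take 11-31% as the saving. Those figures need the clinic-level slope to be known and clinic effects that are not fully stable. Estimating the slope from 21 clinics, or allowing a clinic correlation of 1.0, brings the range down.

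**What to change.** For PANSS, SRFP and QPR, prespecify the 12- and 24-month values as outcomes in the HLM, with arm, time, arm by time and the participant's own baseline score as fixed effects, and with the clinic and participant random effects kept. The clinic mean of the baseline score is optional. Report the adjusted arm difference at each visit with its interval.

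Keep the stated change model as a sensitivity analysis. Do not make a model with a common baseline mean across arms the main analysis, given that recruitment follows allocation.

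The cost is wording only, with no added data collection, and it should be settled before unblinded data are seen. The small downside is that adjustment assumes measured baseline captures any systematic difference between arms. The sensitivity analysis shows how far the result depends on that.

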### Training and supervision

The training approach for the OTCH teams will follow the established training strategies utilized by the OnTrack Central training team at the Center for Practice Innovations, for training teams in the state of New York and nationally [18]. The training will be delivered primarily through an online learning platform that will allow for virtual meetings focused on individualized and group consultation and coaching, didactic webinars, opportunities for sharing and learning from each other, and discussing data to help maximize the quality of the implementation. The OTCH trainers will also be available via email or phone for specific consultation needs that arise over the duration of the program and they will have access and regular meetings with OnTrack Central trainers in New York to help adapt the training strategy to meet the local needs.

OTCH teams will receive an initial, remote training providing a general overview of the treatment model before starting implementation. This allows for an opportunity to discuss practical components of the implementation, understand where each team is at regarding their readiness for implementation of the treatment model and provides an opportunity for engaging in in vivo problem solving to address questions and barriers faced at the individual agencies hosting the programs. Training then continues following a set monthly schedule of role and team-based learning collaborative calls, so that each team receives the same amount of training and information on a regular basis (Table 3). Learning collaboratives have traditionally been used in health care and are increasingly used in behavioral health care [18]. Fundamental elements of a learning collaborative include a number of organizations working together, using quality improvement methods to close the gap between potential and actual performance, learning from experts as well as from one another, and using data to track performance [18]. This will be complemented with resources for self-paced learning that teams can access through the virtual learning platform. Trainers and trainees will also receive site-level data (both related to outcomes and fidelity) that will be utilized during virtual meetings to guide discussions focused on improving the implementation, clarifying questions related to the model, and problem-solve challenges they may be facing.

**Table 3 Tab3:** Description of training approach

Training event	Description

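### The single mediation power figure of over 80% (N=270, a=b=.26) does not hold for fidelity or for any provider score attached by clinic, where the information comes from 21 clinics

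*Protocol article*

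**What the plan says.** The Aim 2a and 2b analyses section sets out to establish "service and implementation outcomes at participant- and provider-level at 12 months as mediators of the OCTH effect" on 24-month symptoms, functioning and recovery. Mediators enter one at a time and then all together. The Aim 1a and Aim 1b section names fidelity, acceptability and uptake as the implementation outcomes, and patient-centeredness, adherence and retention as the service outcomes.

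The sample size section starts from 270 analysed participants and an ICC: "This power calculation was derived assuming an intra-class correlation of 0.05 for outcomes by clinic". For mediation it relies on tabulated sample sizes and concludes that "we have over 80% power to detect a significant mediation effect with path a=.26 and b=.26". It expects path a above 0.35 and mediator-outcome correlations above 0.40. It does not distinguish mediators measured on clients from mediators measured on a service or a provider.

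Table 4 describes fidelity as a rating of how far FEP services deliver evidence-based practice, drawn from provider feedback, supervision calls and site visits. EBPAS and SDM-Q-Doc are completed by providers, and the RSA has provider and client versions.

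**The concern.** If everyone in a clinic carries the same mediator value, then within an arm that value can explain only the between-clinic part of a participant's outcome. The plan sets that part at 5% of the outcome variance. The mediator also has only 21 distinct values, so treating the test as one on 270 observations overstates its information.

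Whether fidelity and provider practice carry the benefit is central to an implementation trial. If the power figure is taken to cover them, a non-significant indirect effect could be read as good evidence against the mechanism when the test had little chance of detecting it.

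**Working it through.** **Inputs from the sample size section.** 270 participants, 21 clinics, ICC 0.05, two-sided alpha 0.05, a=b=.26, d=0.35. **Assumed, because the protocol gives no value:** the share of between-clinic outcome variance that the mediator explains (25%, 50%, 100%), and arm separations in the mediator of 1 and 2 SD.

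**1. The plan's own figure.** I took 270 independent participants, arm coded -1/+1, M = a·arm + error and Y = b·M + error, with residual SD 1 and a=b=.26. In 4,000 simulated trials both paths were significant in 98%, and the Sobel test was significant in 95%. So over 80% is correct in that setting.

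**2. Ceiling for a clinic-wide mediator.** Write Y = arm effect + u + e, with Var(u) = 0.05 and Var(e) = 0.95. Within arm, Cov(M,Y) = Cov(M,u), which is at most sd(M)·sd(u). Hence:
- within-arm |r| ≤ √0.05 = 0.224;
- b in total-SD units at a=.26 ≤ 0.224/√(1 − 0.26²) = 0.224/0.966 = 0.232;
- b in residual-SD units ≤ 0.224/√0.95 = 0.229, whereas b=.26 in those units needs a within-arm r of 0.26/√(1 + 0.26²) = 0.252;
- correlation pooled over arms at d=0.35 ≤ √((0.05 + 0.35²/4)/(1 + 0.35²/4)) = √(0.0806/1.0306) = 0.280.

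A within-arm correlation of .26 would need an ICC of 0.26² = 0.068, and .40 would need 0.40² = 0.16.

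**3. Information in 21 clinics.**
- *Path a.* With equal arms, a=.26 corresponds to a separation of 2(0.26)/√(1 − 0.26²) = 0.54 SD. With 10 and 11 clinics the expected t is about 0.54·√(10·11/21) = 1.23, against a critical value of 2.09 (19 df).
- *Path b.* There are 270/21 = 12.86 participants per clinic, so the variance of a clinic mean is 0.05 + 0.95/12.86 = 0.124, of which 0.05/0.124 = 40% is true clinic variation. If M explains 25%, 50% or 100% of that, its correlation with the clinic mean is √(0.25·0.40) = 0.32, 0.45 or 0.64. The corresponding t values, r√18/√(1 − r²), are about 1.4, 2.1 and 3.5, against 2.10 (18 df).

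**4. Power by simulation.** Clinic-mean regressions, with both paths required to be significant:

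| Arm separation in mediator | 25% explained | 50% | 100% |
|---|---|---|---|
| Path b alone | about 28% | about 53% | about 88% |
| Joint, 0.54 SD (a=.26) | about 6% | about 10% | about 19% |
| Joint, 1 SD | about 15% | about 30% | about 50% |
| Joint, 2 SD | about 28% | about 53% | about 88% |

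In this grid, joint power passes 80% only when the mediator explains all the between-clinic variance and separates the arms by 2 SD.

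**The case against.** A reader might infer that b=.26 and r>0.40 are impossible for fidelity and for every provider score. The documents do not support that, for three reasons.

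- **Attachment of provider scores is not stated.** SDM-Q-Doc asks about a particular consultation, and each OTCH participant is assigned a Primary Clinician, so linkage client by client is conceivable. A linked score varies within clinic and escapes the ceiling. The point covers provider scores only where they are attached by clinic.
- **The ceilings on pooled quantities depend on a and d.** The plan's a=.26 and d=0.35 are detectable values, and it expects larger effects. The cap on b in total-SD units passes .26 once a exceeds about 0.52 (about 1.2 SD), and the pooled correlation can reach 0.40 at d of about 0.72. The plan does not say that its r>0.40 is a within-arm correlation.
- **The ICC of 0.05 is a planning value.** The conflict is between the plan's own assumptions. It is not a fact about the clinics.

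The level of fidelity can also be questioned. Table 4 lists providers, families and participants as its group, and the Background places implementation outcomes at provider and participant level. The training section's "Trainers and trainees will also receive site-level data (both related to outcomes and fidelity" does not settle it, because outcomes are called site-level there too. Still, Table 4 defines the scale as a rating of services, so a clinic-wide score is the natural reading.

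The protocol nowhere says that a non-significant result will be reported as no mediation, and it plans bootstrap intervals and sensitivity analyses. These points limit the reach of the concern but do not rescue the power figure. The simulation already includes larger separations, and at 1 SD it still gives only about 15% to 50%.

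**Conclusion.** The stated power is wrong for fidelity, and for any provider score attached by clinic. At the plan's a=.26, joint power is about 6% to 19%. At 1 SD separation it is about 15% to 50%. The required b=.26 exceeds the ceiling of about 0.23 at that a.

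This rests on the plan's ICC of 0.05, on fidelity being one score per clinic, and on the assumed variance shares and separations. It was computed with clinic-mean regressions rather than the planned structural equation model, but that model would draw on the same 21 mediator values.

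It would go too far to say that the design can never show mediation through fidelity, or that these mediators must be dropped from Aim 2b: in the most favourable case joint power is about 88%. The ceiling does not apply to client-measured mediators. The check in step 1 treated clients as independent, and how clustering affects those mediators was not examined here. The main arm comparisons are untouched.

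**What to change.** In the sample size section, limit the statement of over 80% power to mediators measured on each client: CollaboRATE, participant RSA, participant service-receipt items, YSS, BARS and retention. State separately, on 21 clinics, the much lower power for fidelity and for any provider score attached by clinic, with the assumed variance share and arm separation. Say for each provider score whether it is attached by clinic or linked client by client.

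In Aim 2b, label the clinic-wide mediation results exploratory, report estimates with confidence intervals, and state that a non-significant result is not evidence of no mediation.

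The change is to wording only; data collection stays as it is. The cost is a less favourable power statement for these mediators.

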**Fig. 3 Fig3:**
[figure not shown]
Conceptual model for analysis

We will carry out all analyses on an Intention-to-treat basis. All tests will be two-sided with critical value *α*=0.05. Prior to analysis, we will examine all variables for outliers and inconsistencies and examine their distributions. The distributions of all continuous variables will be checked for normality, and transformations will be employed to normalize distributions, if necessary, before applying specific parametric techniques. Missing data will be imputed, using multiple imputation procedures in standard statistical software (e.g., Stata or SAS).

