We will examine multilevel factors that may moderate the implementation of OTCH (see Table 1). (1) *Community level*: there is evidence that access to and engagement with mental health services is low among those who reside in poor communities [41]. (2) *Provider level*: we hypothesize that more positive attitudes toward evidence-based practices and recovery orientation will be associated with more successful implementation of programs which have these characteristics like OTCH [42]. (3) *Participant level*: we also hypothesize that socio-demographics and baseline clinical state will be predictors of implementation and service outcomes based on prior studies with clinical outcomes [17]. We will test this aim by including all three types of moderators into the HLM utilized for Aim 1.a. Specifically, because we aim to test whether these factors differentially affect the implementation of the OTCH compared to FEP usual care (i.e., an interaction with treatment), we will incorporate a random intervention effect into the HLM and allow the factors to predict the random intervention effect at both the clinic and participant level. The magnitude and statistical significance of the beta coefficients for these factors will provide the test of them as treatment effect moderators.

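### The Aim 2b mediation model, as described, adjusts for no baseline clinical score, although the protocol expects baseline clinical state to predict the participant-level mediators

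*Protocol article*

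**What the plan says.** All places are in the protocol article.

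- **Aim 2a and 2b analyses.** Beyond the Aim 1a and 2a intervention effects, "we must also establish that service and implementation outcomes at 12 months are associated with better participant symptoms, functioning, and recovery orientation at 24 months". Mediation is then quantified as the total effect minus the direct effect, fitted by structural equation model in Mplus and tested by bootstrap. Mediators enter one at a time and then together. No baseline variable is named. On confounding, the section speaks of time-varying confounders, says that recent developments "suggest the need for sensitivity analyses to explore the potential impact of unmeasured confounders", and commits to those analyses.
- **Aim 1a and Aim 1b analyses.** The protocol hypothesises that "socio-demographics and baseline clinical state will be predictors of implementation and service outcomes". Those outcomes are the Aim 2b mediators.
- **Sample size and power analysis.** The mediation argument closes with "assuming no confounding of mediator-outcome relationship".
- **Table 4.** PANSS, SRFP and QPR are measured at baseline, 12 and 24 months. CollaboRATE, participant RSA, YSS and BARS also have baseline values. Retention is counted from randomization and has none.

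**The concern.** Randomization protects the effect of OTCH on the mediator (path a). It does not protect the association of the 12-month mediator with the 24-month outcome (path b). If baseline clinical state predicts the mediator, as the protocol expects, and also predicts the same clinical scale two years later, as is plausible, it is a measured common cause of both. Leaving it out makes path b non-zero even when the mediator does nothing.

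Participants who start less ill may rate services higher, adhere better and be better at 24 months whatever the service does. If OTCH also raises those ratings, Aim 2b could name shared decision-making, adherence or retention as the mechanism when the benefit came by another route.

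The existing provisions do not cover this. The sensitivity analysis concerns what was not measured. The Aim 1a covariate rule is triggered by baseline differences between arms, and balance between arms says nothing about mediator-outcome confounding.

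**Working it through.** **Inputs from the protocol article.** N = 270 with follow-up; ICC 0.05; at least 10 clinics per arm (20 clinics in most of the simulations, 21 in some); two-sided alpha 0.05; path a "Path a is expected to be >0.35 (argued for Aim 1 above"), taken here as d = 0.35.

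**Assumed, because the article gives no values.** Baseline-mediator correlation r = 0.1 to 0.4; baseline correlation with the 24-month score s = 0.5 unless stated.

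**1. The plan's own figure.** It says "we have over 80% power to detect a significant mediation effect with path a=.26 and b=.26". With standardized paths, no confounding and no clustering, simulation gives 98% (percentile bootstrap) or 99% (bias-corrected), so the statement holds. Read as Cohen's d, a = 0.26 gives only 57–63%; d = 0.35 with b = 0.26 gives 81–86%. None of these allows for confounding.

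**2. Bias in path b when the mediator has no effect.** With mediator and outcome scaled to variance 1 within arm, the unadjusted path b equals r × s. At s = 0.5 this is 0.05, 0.10, 0.15 and 0.20 for r = 0.1, 0.2, 0.3 and 0.4.

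**3. Hand check of the false-positive rate, ignoring clustering.** The indirect effect is significant roughly when both paths are.
- Path a: SE = 2/√270 = 0.122; z = 0.35/0.122 = 2.88; probability significant 0.82.
- Path b: SE = √[(1 − (rs)²)/267] ≈ 0.061; z = 0.82, 1.64, 2.48 and 3.34; probability significant 0.13, 0.37, 0.70 and 0.91.
- Product: about 11%, 31%, 57% and 75%.

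**4. Simulation of the bootstrap test, d = 0.35, s = 0.5, true mediator effect zero.** Ranges span repeated runs with ICC 0 or 0.05, using 400–500 trials per cell where stated (Monte Carlo error up to about 2.5 points).

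| r | Baseline omitted | Baseline in both equations |
|---|---|---|
| 0.1 | 11–13% | 3–7% |
| 0.2 | 25–31% | 3–7% |
| 0.3 | 52–60% | 3–7% |
| 0.4 | 69–75% | 3–7% |

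With r = 0 the unadjusted rate is 3–6%. With r = 0.1 and s = 0.3 it is only 5–8%. With r = 0.4 and s = 0.6 it reaches 71–97% over d = 0.35 to 0.8. Using change from baseline as the outcome does not cure it: about 8–88% over the cells with r > 0 (d = 0.35 or 0.5).

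**5. The full rule.** Here the effect on the mediator, the total effect on the outcome and path b must also be significant. ICC 0.05, d = 0.35, s = 0.5, with these extra tests ignoring clustering:

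| r | No clinical effect of OTCH | Direct effect 0.35 SD |
|---|---|---|
| 0.1 | 0.4% | 9.8% |
| 0.2 | 2.2% | 21.6% |
| 0.3 | 6.6% | 37.4% |
| 0.4 | 6.8% | 55.2% |

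Over the wider grid (d = 0.35 or 0.5; r = 0.1 to 0.4; s = 0.3 to 0.6) the two columns span about 0–11% and 4–70%. When Aim 1a and 2a effects are tested at clinic level, closer to the planned models with clinic random effects, the rates for r = 0.2–0.4 are 0.7–5% and 12–44%. A further run of the full rule gave about 0–2% and 5–38%.

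**The case against.** **The article is silent; it does not exclude.** A reader might infer that baseline scores are barred from the model. The text does not say so. It is a condensed article, and covariate lists are commonly left to a fuller document that is not shown. This stands, and the point is limited to the model as described. But the section does fix the criterion, estimand, software, model variants and test without a baseline variable, and the expectation about baseline clinical state conflicts with the no-confounding assumption in the same article.

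**The bootstrap rates are not the rate at which mediation would be declared.** A reader might take the table in step 4 as that rate. The protocol also requires Aim 1a and 2a effects. With no clinical effect of OTCH this largely contains the error. It does not when OTCH benefits patients by another route, and clinical benefit is what the protocol expects.

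**Confounding is acknowledged.** It is wrong to say that the plan ignores it. A sensitivity analysis for unmeasured confounders arguably presupposes adjustment for measured ones, and the no-confounding phrase is a caveat on power, not an analysis rule. Both are fair. The presupposed adjustment is nevertheless not stated.

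**Not all mediators are affected alike.** Fidelity, EBPAS and SDM-Q-Doc vary mainly by provider or clinic. The participant-level calculation does not carry over to them.

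**Conclusion.** The point holds for participant-level mediators: CollaboRATE, participant RSA, YSS, BARS and retention. If the model is fitted as described and baseline clinical state predicts both mediator and outcome, path b is biased and the indirect-effect test loses its nominal error rate. At d = 0.35 and s = 0.5, false significance of the bootstrap test runs from about 11% (r = 0.1) to 69–75% (r = 0.4), against about 5% after adjustment.

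Under the full rule, false mediation is near or below 5% in most cases (at most about 11%) if OTCH has no clinical effect. It is roughly 5–40%, and up to 70% in the strongest scenarios, if OTCH has a direct effect of 0.35 SD.

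These sizes rest on assumed correlations. The protocol gives neither their size nor their direction, so no single error rate can be attached to this trial. Aim 2b is a stated aim but not the primary comparison, so this should be corrected without calling the main results into question.

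**What to change.** In the Aim 2b text, state that for participant-level mediators both the mediator equation and the outcome equation adjust for:

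- the baseline value of the clinical outcome analysed (PANSS, SRFP or QPR);
- the baseline value of the mediator where it is collected (not available for retention);
- if wanted, a short pre-specified set of further baseline covariates. Entering every socio-demographic item of Table 4 is unnecessary and would be heavy in the all-mediators model with 21 clinics.

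Reconcile this with the hypothesis under Aim 1b and the no-confounding assumption in the power section. Keep the sensitivity analysis for what remains unmeasured.

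The cost is wording and a few extra model parameters; the scores named above are already collected.
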